## Abstract

**Background:**

Chinese herbal medicine is one of the most popular Chinese medicine (CM) therapies for primary insomnia. One of the important characteristics of CM is that different Chinese clinicians give different prescriptions even for the same patient. However, there must be some fixed drug patterns in every clinician’s prescriptions. This study aims to screen the effective core drug patterns in primary insomnia treatment of three prestigious Chinese clinicians.

**Methods/design:**

A triple-blind, randomized, placebo-controlled, parallel-group clinical trial will be performed. Three clinicians will diagnose and treat every eligible patient individually and independently, producing three prescriptions from three clinicians for every patient. Patients will equally be randomized to one of four groups – medical group A, medical group B, medical group C, or placebo group – and observed for efficacy of treatment. The sample will include primary insomnia patients meeting DSM IV-TR criteria, Spiegel scale score >18, and age 18 to 65 years. A sequential design is employed. Interim analysis will be conducted when between 80 and 160 patients complete the study. The interim study could be stopped and treated as final if a statistically significant difference between treatment and placebo groups can be obtained and core effective drug patterns can be determined. Otherwise, the study continues until the maximum sample size reaches 300. Treatment of the CM group is one of three Chinese clinicians’ prescriptions, who provide independently prescriptions based on their own CM theory and the patient’s disease condition. Assessment will be by sleep diary and Pittsburgh sleep quality index, and CM symptoms and signs will be measured. Primary outcome is total sleep time. Assessment will be carried out at the washout period, weeks 1, 2, 3, and 4 and 4th week after the end of treatment. Effectiveness analysis will be per intent to treat. A multi-dimension association rule and scale-free networks method will be used to explore the effective core drug patterns.

**Discussion:**

The effective core drug patterns will be found through analyzing several prestigious CM clinicians’ treatment information. Screening the effective core drug patterns from prestigious clinicians can accelerate the development of new CM drugs.

**Trial registration:**

NCT01613183

## Background

Insomnia is a common public health problem. Approximately one-third to one-quarter of the population in developed nations has been reported to have sleep disturbance problems to some extent in their lives and approximately 10% suffer from persistent insomnia [1]. Population-based studies suggest that about 30% of the total population complains of sleep disruption, while approximately 10% has associated symptoms of daytime functional impairment with the diagnosis of insomnia, although it is unclear about the proportion among the 10% of population really suffering from chronic insomnia [2]. Pharmacologic therapy is the main treatment of insomnia. However, most of the drugs prescribed for insomnia have some risk of overdose, tolerance and addiction. Long-term use of frequently prescribed medications (for example, benzodiazepines) can lead to habituation and problematic withdrawal symptoms [3]. In China, most of patients prefer to receive traditional Chinese medicine (CM) treatment, including Chinese herbal medicine, acupuncture, massage and cupping [4-12]. In recent years, the traditional CM therapy for insomnia is enjoying increasing popularity in the West [5,6,13,14], reflecting growing acceptance of such treatments even in the West. Chinese herbal medicine is one of the most popular CM therapies for insomnia.

However, it is a common phenomenon that the efficacy of Chinese herbal drugs is related to the clinician. In other words, the efficacy of CM varies with different clinicians. Prestigious Chinese clinicians may therefore have some patterns in the treatment of insomnia. In our previous studies, we have observed some core drug patterns of prestigious clinicians in treatment of insomnia [15,16]. But these previous studies have some shortcomings. On the one hand, the studies are retrospective and the data were collected from daily actual clinical treatment information of prestigious clinicians. In this case, the data quality cannot be guaranteed. On the other hand, the treatment efficacy of prestigious clinicians was not validated and needed confirmation in further study. This study aims to screen the effective core drug patterns of prestigious Chinese clinicians in treatment of primary insomnia.

### Objectives

The objective of this study is to screen the effective core drug patterns in primary insomnia treatment with Chinese herbal medicine by a triple -blind, randomized, placebo-controlled trial.

## Methods

### Design

This is a triple-blind (with patients, clinicians, outcome assessors blinded), randomized, placebo-controlled, parallel group clinical trial. Figure 1 shows the trial design and Table 1 summarizes the timing of the trial.

**Figure 1 F1:**
[figure not shown]
Trial design.

**Table 1 T1:** Calendar summary

**Period**	**Screening**	**Washout**	**Treatment**				**Follow-up**
**Week(W)**	**-1 W**	**0 W**	**1 W**	**2 W**	**3 W**	**4 W**	**4th week after the end of treatment**
Inclusion and exclusion criteria	×						
Informed consent	×						
Demography	×						
Past Medical history & treatment history	×						
Spiegel Scale	×	×					
Self-rating Anxiety Scale	×	×				×	
Beck Depression Inventory	×	×				×	
http://Pittsburgh Sleep Quality Index	×	×	×	×	×	×	×
CM syndromes and signs	×	×	×	×	×	×	×
Sleep diary	×	×	×	×	×	×	
Prescription (include every herb and dose)			×	×	×	×	
Vital signs	×	×	×	×	×	×	
Adver event		×	×	×	×	×	

### Randomization

Three Chinese clinicians will diagnose and treat every eligible patient individually. Every Chinese clinician will provide CM patterns and the prescription according to every patient’s disease condition. There will therefore be three prescriptions from three Chinese clinicians for every patient at every visit. At the first visit, patient will equally be randomized to one of the following four groups: medical group A, medical group B, medical group C or placebo group. Patients in the CM groups will be given one of three Chinese clinicians’ prescriptions. Patients in the placebo group will be given the placebo simulating the core drug patterns in the previous study. In the whole study, the randomization of group assignment only occurs at the first visit, and the randomization results will be applied to the following visits. In other words, although the patients have to be diagnosed by every clinician for every visit, they always receive the drug prescribed by the clinician who is distributed to them by randomization at the first visit or they receive placebo. Furthermore, in order to avoid the potential bias, every patient’s order to visit three clinicians is randomized at every visit, meaning that the visiting order in which one patient visits the clinicians may be different every time. It is worth mentioning that a web central randomization system is employed to guarantee the quality.

### Chinese medicine groups

After randomization, patients in the CM groups are to receive one of three Chinese clinicians’ prescriptions. Every Chinese clinician diagnoses the patients and prescribes individually based on patients’ syndrome differentiation and their own CM experiences. During the whole treatment, Chinese clinicians can make necessary adjustment in their medicinal prescription depending on the condition of the disease. The prescriptions of Chinese clinicians are pure Chinese herbs.

### Placebo group

Patients in the placebo group will receive the dummy of the core drug patterns obtained in a previous retrospective study. The previous core drug patterns include Fried semen Ziziphi Spinosae, Tuckahoe, Preparation of Polygala, Chinese Angelica root, Lotus heart, White peony root, dried tangerine peel, acorus calamus, Coptis chinensis, and Licorice health.

All CM is a herbal concentrate-granule, not a decoction. The herbal concentrate-granule, a product of high quality that can be intensively produced on a large scale, possesses many advantages, such as small dosage, easy to use and good effectiveness in clinical application. The quality of a herbal concentrate-granule can be controlled with mechanization. In China, the herbal concentrate-granule is widely accepted [17].

The placebo medicine dummy is produced by the Pharmacy Department of Guang’anmen Hospital, China Academy of Chinese Medical Sciences. The placebo is also a herbal concentrate-granule, and is similar to the true CM concentrate-granule in the aspects of color, taste, smell and package. According to the theory of CM, the prescriptions will probably be adjusted at different visits based on the patient’s disease condition. To achieve better blinding, four kinds of placebos with different tastes will therefore be designed for different visits.

One bag of herbal concentrate-granule is taken two times daily one and half hour after breakfast and dinner, respectively.

### Eligibility criteria

#### Inclusion criteria and exclusion criteria

Patients are eligible to participate if they are aged between 18 and 65 years, and meet the definition of insomnia from the *Diagnostic and Statistical Manual of Mental Disorders*, Fourth Edition, Text Revision, with Spiegel scale >18. It is imperative that patients should read and sign an informed consent form to participate in the trial.

The following exclusion criteria are observed: total sleep time <2 hours, secondary insomnia, Self-rating Anxiety Scale score >60, Beck Depression Inventory score <8, complicated with hypertension, diabetes, stroke, and coronary heart disease, having drug abuse history, pregnancy or preparing for pregnancy, and participating in another clinical trial at the same time.

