## Discussion

The discovery of a new effective prescription in clinical practice is key to the development of new CM. The experiences of prestigious Chinese clinicians are the main source of effective CM. However, the discovery of effective core drug patterns mainly depends on the accumulation of clinicians’ experiences and is always a long process. This study proposes one method used to develop new effective core drug patterns based on the prestigious clinicians’ treatment data. Randomization, placebo control and blinding designs are employed in the study, where three prestigious Chinese clinicians are treated as subjects. To minimize the bias and factitious influence, a web central randomization system and a clinical research data-capture computer system are adopted to assign the group and collect the data, respectively. In the study, we can obtain one or several effective core drug patterns. Unlike previous retrospective studies [15,16], this perspective study has strictly tested the efficacy of Chinese herbal medicine through comparison between a treatment group and a placebo group. Because the exploratory analysis of core drug patterns is based on the effective patients, the results should be more accurate and useful. In a word, the analysis can accelerate and improve the development of new Chinese herbal medicine for discovery of new effective core drug patterns through exploring the treatment data of prestigious CM clinicians.

To guarantee the quality of the study and accuracy of core herb patterns obtained, patients who met the diagnosis of primary insomnia were recruited. In addition, those patients with hypertension, diabetes, stroke and coronary heart diseases are excluded because these patients may demonstrate mixed symptoms or syndromes in the diagnosis that affect the accuracy of prescriptions by clinicians. Patients older than 65 are easily complicated with the diseases mentioned above and then excluded from the study.

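### The Beck Depression Inventory exclusion (<8) runs in the opposite direction to the anxiety exclusion beside it and conflicts with the primary-insomnia population

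*Protocol article*

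**What the plan says.** In the protocol article, under Inclusion criteria and exclusion criteria, the list of reasons to keep a patient out begins "The following exclusion criteria are observed: total sleep time <2 hours" and continues with "secondary insomnia, Self-rating Anxiety Scale score >60, Beck Depression Inventory score <8". The BDI item is therefore an exclusion, not an inclusion.

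The target population is primary insomnia. The Abstract and the Objectives both say so, and the Discussion states that "patients who met the diagnosis of primary insomnia were recruited".

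The BDI appears in only two other places. Table 1 schedules it at screening, at week 0 and at week 4, and the Abbreviations list expands the acronym. Neither place gives a threshold, an upper limit, a scoring direction or a reason for requiring depressive symptoms.

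**The concern.** An exclusion based on a depression scale in a primary-insomnia trial would be expected to remove high scorers. This one removes low scorers. Anyone who applies the printed rule turns away patients with few or no depressive symptoms, and the BDI item itself stops nobody above the threshold.

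The stake is who enters the trial. Its main product is a set of herb patterns mined from prescriptions that each clinician fits to the individual patient's syndromes and signs. If entry requires depressive symptoms, the prescriptions are written for a population selected on those symptoms. Analysis could not repair this, because no patient with a score below 8 would be in the data. If screening in fact uses a different rule, the published eligibility statement misdescribes the population. The sponsor has something to correct in either case.

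**Working it through.** No sample size, power or alpha figure is involved. The check is a logical one on the text.

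**Inputs**

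- BDI item, in the exclusion list: "Beck Depression Inventory score <8".
- Anxiety item, same sentence: "Self-rating Anxiety Scale score >60".
- Sleep-time item, same list: "The following exclusion criteria are observed: total sleep time <2 hours".
- Secondary insomnia is a separate exclusion in the same sentence.
- Population: primary insomnia (Abstract, Objectives, Discussion).
- Assumptions, not stated in the article: a higher BDI means more depressive symptoms, a higher SAS means more anxiety, and BDI scores are whole numbers from 0 upward.

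**Step 1: direction of each scaled exclusion**

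| Item | Who is removed | End of the scale removed |
|---|---|---|
| Total sleep time <2 hours | shortest sleepers | severe |
| SAS >60 | highest anxiety scores | severe |
| BDI <8 | lowest depression scores | mild or none |

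The BDI item is the only one of the three that removes the mild end.

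**Step 2: what each possible reading admits on the BDI item alone**

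| Reading | Fails the item | Passes the item |
|---|---|---|
| As printed: exclude if <8 | 0 to 7 | 8 and above, no upper limit |
| Sign reversed: exclude if >8 | 9 and above | 0 to 8 |
| Inclusion limit in the wrong list: include if <8 | 8 and above | 0 to 7 |

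The printed rule shares only the score of exactly 8 with the sign-reversed reading, and no score at all with the misplaced-inclusion reading. The two candidate corrections differ from each other only at a score of 8. The last two rows keep the printed number for illustration; the article does not confirm that 8 is the intended cut-off.

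**Step 3: consistency with the rest of the eligibility set**

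Excluding secondary insomnia and high anxiety keeps out patients whose sleep complaint may stem from another condition. A depression item with that purpose would remove high scorers. The printed item leaves them to be caught, if at all, by the secondary-insomnia and SAS exclusions.

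**Step 4: effect on the comparison between arms**

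The BDI is taken at screening and at week 0, and allocation happens at the first treatment visit. The rule therefore acts before randomization and equally on all four arms. It changes who is compared, not the fairness of the comparison.

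**The case against.** The strongest reply is that this looks like a misprint in a condensed article. The full protocol and the screening form are not shown. Screening is done by a designated clinician outside the trial team, who applies a primary-insomnia diagnosis whatever the BDI says, and nothing in the article shows that anyone was screened by the printed rule. This stands as a limit on the claim: harm follows only if the rule is used as printed. It does not remove the point, because the article states an operative entry threshold and states it in a direction that conflicts with its own population.

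Four stronger readings may tempt a reader, and the article does not support them.

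- *Every depressed patient would be admitted.* This holds for the BDI item taken alone. The secondary-insomnia and SAS exclusions could still remove some.
- *Most or typical primary-insomnia patients would fail screening.* That needs a BDI distribution in this population, which the article does not give. Saying that all entrants would score 8 or more only restates the inequality.
- *The Discussion's rationale covers depression.* Its remark that "these patients may demonstrate mixed symptoms or syndromes in the diagnosis that affect the accuracy of prescriptions by clinicians" refers to four named physical diseases and does not mention depression. The Discussion supports the point only by naming primary insomnia as the population.
- *The sign is certainly reversed.* A limit placed in the wrong list fits the text equally well.

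**Conclusion.** The point holds as an internal contradiction in an operative eligibility rule. As printed, the BDI item excludes scores of 0 to 7 and sets no ceiling, which is opposite in direction to the SAS item in the same sentence and at odds with a primary-insomnia trial. No passage resolves it.

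The size is logical, not numerical: the printed rule and either candidate correction admit populations that overlap at a single score or not at all. No planned sample size, power or alpha changes, and the comparison of Chinese medicine with placebo is not biased. What is exposed, if the rule is applied as printed, is the target population, generalisability and the relevance of the mined herb patterns.

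The conclusion assumes the standard scoring direction of the BDI. It does not assume that anyone was wrongly enrolled. The item still has to be corrected, because it decides who enters and whose prescriptions are mined.

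**What to change.** 1. Check the full protocol and the screening form to establish whether the sign is reversed or the item is an inclusion limit placed in the wrong list, and what cut-off was intended, including how a score exactly at the cut-off is treated.
2. Reconcile the BDI criterion with the SAS and secondary-insomnia exclusions and with the primary-insomnia population. Correct it in the protocol, the screening form and anywhere else it is used.
3. Check the screening BDI of anyone already enrolled against the corrected criterion and document any mismatch.

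No cut-off is proposed here, because the article does not establish one. The cost is a correction to one line of text and the matching forms, plus a review of scores that Table 1 already schedules at screening. If a requirement for depressive symptoms was in fact intended, the protocol should say so, give the reason and describe the population accordingly.

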### Recruitment/consent procedures

Patients are recruited by means of poster at clinic. The patient screening is conducted by the specified clinician who doesn’t participate in the study. If a patient meets the study criteria, the clinician responsible for patient screening will provide him or her with written information, explaining the study in detail in an understandable language, and obtain written consent if he or she agrees to take part in the study. All patients’ informed consent must be obtained. Any patient cannot be enrolled if she/he refuses or shows significant distress.

### The procedure of study

In the washout period, an eligible patient who has signed informed consent will receive placebo for 1 week (washout period) in order to eliminate the influence of drugs taken before the study. In the treatment period lasting 4 weeks and including four visits, each of three Chinese clinicians will independently provide a disease pattern and prescription for every patient. Three generated prescriptions will then be passed on to the pharmacy. However, whether one patient receives one of three prescriptions or placebo is dependent on the result of randomization that is conducted by the authorized person using a central randomization system at the first visit.

When a patient returns to the hospital once a week after the first treatment, a professional clinician will conduct an assessment on efficacy. The patient will then receive the secondary treatment from three Chinese clinicians, repeating the same procedure as the first one. The whole study will last 9 weeks, including 1-week washout, 4-week treatment, and follow-up happening at the 4th week after the last treatment.

All three Chinese clinicians are experts on insomnia in Prestigious Chinese Clinician Research Laboratory of Guang’anmen Hospital, China Academy of Chinese Medical Sciences. In order to minimize potential bias and to keep the blind condition of study as possible as one can, all researchers participating in the study are divided into three groups: clinical study group, diagnosis and assessment group, and quality control and statistical analysis group. In the quality control group, there are two persons (the corresponding authors) are responsible for the management and early stopping of the trial. A clinical research data capture computer system is applied to collect the data in this study.

The study was approved by the Institutional Review Board of the Institute of Basic Research in Clinical Medicine, China Academy of Chinese Medical Sciences. The approval number is 2011NO6.

### Assessment

The investigator carrying out the efficacy assessment will be blinded to which treatment the patients received. The visits and assessments will take place at screening, washout period, weeks 1, 2, 3, 4 after treatment, and the 4th week after the last treatment. All assessments will be conducted by the clinicians of the diagnosis and assessment group.

### Primary efficacy indicator

#### Total Sleep Time (TST)

In this study, the major indicator is the total sleep time (TST), which is assessed according to the sleep diary. All patients are required to record their sleeping information in detail every day. The sleep diary contains the following information: the time a patient goes to bed and gets out of bed; the time a patient thinks sleep onset occurs; the presumed cause, number, time, and length of any nighttime awakenings and activities during these moments; the name, dosage and time of any drugs used, including medication, sleep aids, caffeine and alcohol, and so forth; and activities happening 3 hours before bedtime, such as meditation, watching television, playing PC games, exercise, and so forth.

The efficacy can be confirmed only when improvement in TST is >0.5 hours and is considered statistically significant. Normally, the participants are not allowed to take any pharmacologic medicine used to treat insomnia. However, they are allowed to do so if they could not bear the bitterness brought about by insomnia. Under such circumstances, the dosage and the name of the medicine must be recorded carefully in sleep diaries.

### Secondary efficacy indicators

The secondary efficacy indicators include sleep onset latency, wake time after sleep onset, sleep efficiency, Pittsburgh sleep quality index (PSQI) and CM symptoms and signs. Sleep onset latency, wake time after sleep onset and sleep efficiency are obtained from the sleep diary. The Chinese-version PSQI is employed to measure the quality of sleep. The PSQI is a self-rated questionnaire used to assess sleep quality and disturbances over a 1-month time interval. Nineteen individual items generate seven component scores: subjective sleep quality, sleep latency, sleep duration, habitual sleep efficiency, sleep disturbances, use of sleeping medication, and daytime dysfunction.

Many studies have demonstrated that the Chinese-version PSQI is a sensitive, reliable, and valid tool to assess the quality of sleep [18,19]. In addition, CM symptoms and signs will be assessed. The main symptoms and signs include headache, dizziness, spontaneous sweating, night sweating, dreaminess, amnesia, anorexia, lassitude of spirit and lack of strength, oppression in the chest, daytime sleepiness, irritability, palpitations, epigastric fullness, tinnitus, thirst, bitter taste in the mouth, abundant sputum, yellow urine, dry stool, sloppy stool, pulse condition, and tongue manifestation.

